# Prevention of doxorubicin-induced Cardiotoxicity by pharmacological non-hypoxic myocardial preconditioning based on Docosahexaenoic Acid (DHA) and carvedilol direct antioxidant effects: study protocol for a pilot, randomized, double-blind, controlled trial (CarDHA trial)

**DOI:** 10.1186/s13063-019-3963-6

**Published:** 2020-02-04

**Keywords:** CarDHA, Chemotherapy-induced cardiotoxicity, Anthracyclines, Carvedilol, DHA, Study protocol

## Abstract

**Background:**

Anthracycline-induced cardiotoxicity (AIC), a condition associated with multiple mechanisms of damage, including oxidative stress, has been associated with poor clinical outcomes. Carvedilol, a β-blocker with unique antioxidant properties, emerged as a strategy to prevent AIC, but recent trials question its effectiveness. Some evidence suggests that the antioxidant, not the β-blocker effect, could prevent related cardiotoxicity. However, carvedilol’s antioxidant effects are probably not enough to prevent cardiotoxicity manifestations in certain cases. We hypothesize that breast cancer patients taking carvedilol as well as a non-hypoxic myocardial preconditioning based on docosahexaenoic acid (DHA), an enhancer of cardiac endogenous antioxidant capacity, will develop less subclinical cardiotoxicity manifestations than patients randomized to double placebo.

**Methods/design:**

We designed a pilot, randomized controlled, two-arm clinical trial with 32 patients to evaluate the effects of non-hypoxic cardiac preconditioning (DHA) plus carvedilol on subclinical cardiotoxicity in breast cancer patients undergoing anthracycline treatment. The trial includes four co-primary endpoints: changes in left ventricular ejection fraction (LVEF) determined by cardiac magnetic resonance (CMR); changes in global longitudinal strain (GLS) determined by two-dimensional echocardiography (ECHO); elevation in serum biomarkers (hs-cTnT and NT-ProBNP); and one electrocardiographic variable (QTc interval). Secondary endpoints include other imaging, biomarkers and the occurrence of major adverse cardiac events during follow-up. The enrollment and follow-up for clinical outcomes is ongoing.

**Discussion:**

We expect a group of anthracycline-treated breast cancer patients exposed to carvedilol and non-hypoxic myocardial preconditioning with DHA to show less subclinical cardiotoxicity manifestations than a comparable group exposed to placebo.

**Trial registration:**

ISRCTN registry, ID: ISRCTN69560410. Registered on 8 June 2016.

## Background

Owing to improvements in antineoplastic treatments, overall cancer survival has improved substantially [1]. Nevertheless, these improvements have been associated with increased incidence of chemotherapy-related side effects. Anthracycline-induced cardiotoxicity (AIC) is a major cause of cancer survivor morbidity and mortality [2–4], particularly when patients develop heart failure (HF) [5]. AIC-induced HF outcomes are worse than other forms of HF and response to conventional therapy can be lower, especially in cases of late detection [6], with a 2-year mortality rate of up to 50% [7]. This contrasts with positive cancer therapy results where, for example, breast cancer mortality has dropped to sit near 10% today [8, 9].

As AIC has been historically associated with left ventricular systolic dysfunction (LVSD), the incidence of AIC has been mainly expressed as a decline in different quantitative left ventricular ejection fraction (LVEF) criteria [3, 10]. AIC-induced clinical LVSD incidence ranges around 9%, where 98% of cases develop during the first 12 months (median time 3.5 months) [6], and subclinical manifestations can reach 27% in 5 years [11]. However, this does not mean that AIC is not associated with other pathological manifestations, such as arrhythmias and biomarker elevation, where incidents of > 12% and 30–35% have been reported, respectively [12].

Evidence has shown that mitochondrial-generated reactive oxygen species (ROS) have a key role in the development and progression of AIC [13–17]. Doxorubicin tends to accumulate in cardiac mitochondria [18]. Inhibition of the enzyme topoisomerase 2β (Top2β) by doxorubicin would be the initiating event of mitochondrial dysfunction with the subsequent generation of ROS, promoting apoptosis and cardiac remodeling, key events in the development of AIC [14, 19].

The role of oxidative stress in AIC has encouraged the evaluation of several direct antioxidant strategies, without satisfactory results except in the case of carvedilol [20]. This β-blocker has uncommon ROS-suppressive properties [21], showing mixed results in trials [22–26] and observational studies [27]. Recently, a clinical trial with carvedilol in 200 patients (CECCY trial) failed to prevent a ≥ 10% reduction in LVEF at 6 months [26]. Nevertheless, the carvedilol group showed a reduction in the increments and peak levels of serum troponin I (TnI), trends towards a lesser increase in left ventricular diastolic diameter and a reduction in the percentage of patients with diastolic dysfunction.

Although β-blocker action cannot be ruled out as playing a role in AIC prevention, the cardioprotective effect from carvedilol is reported to be caused by its antioxidant properties [28–31]. A recent meta-analysis, designed to evaluate efficacy of β-blockers for primary prevention of anthracycline-derived LVSD, also suggested that the antioxidant properties of certain β-blockers could explain the efficacy observed in some trials [32]. As traditional orally administered ROS scavengers have failed to prevent AIC [20], it can be hypothesized that carvedilol advantages in AIC prevention over other potential orally administered antioxidants, may be due to carvedilol’s capacity to reach higher concentrations in cardiac cells [30].

Different factors could explain the variability of carvedilol efficacy in studies. At a mechanistic level, if the cardioprotection was hypothetically given only due to an antioxidant non-specific mechanism [33], a greater individual variability response could be expected than if the effect were a product of a specific β-blocking interaction. At a methodological level, study weaknesses, such as being observational, open-labeled, single-blind, combining cardiovascular drugs, or having a small sample size probably favored mixed results [26, 34]. High heterogeneity of studies with regard to an accumulated dose of anthracycline, cardiovascular risk factor profile, chemotherapy protocols and the involved population, as well as a high individual variability in anthracycline bioavailability and metabolism [35–37] can also be involved. The use of LVSD event based on echocardiographic consensus criterion (post-chemotherapy LVEF decline ≥ 10% to < 50%) as an AIC event to define the primary endpoint, could also be related with inconsistency in results. As several of the latter factors determine AIC incidences, they could partly explain different carvedilol efficacies among protocols, because it is expected that populations with higher AIC incidences have been more prone to benefit from cardioprotection. For example, the CECCY trial, despite its robustness, presented two methodological aspects that together make it difficult to appreciate carvedilol-induced LVSD attenuation: (1) having defined a cardiotoxicity event as a decline in LVEF ≥ 10% through the use of echocardiography (ECHO); and (2) having an event incidence lower than the originally estimated. The use of cardiac magnetic resonance (CMR) instead of ECHO plus a redefinition of the cardiotoxicity event to a drop of less than 10% of the LVEF probably would have allowed CECCY trial to appreciate carvedilol effects at cardiac function level.

Substances with indirect antioxidant properties, both by reducing cellular ROS production (such as iron chelators) and by increasing endogenous antioxidant capacity (such as cardiac preconditioning), are an option to be assessed for primary AIC prevention. However, owing to the nature of the mechanisms involved, these therapies are not exempt of risk. Dexrazoxane, an iron chelator has shown cardioprotective effects [38], nevertheless, it may cause myelosuppression and potential inhibition of doxorubicin antineoplastic efficacy [39–41]. Cardiac ischemic preconditioning has a broad preclinical base in cardiology, but it is usually complex to implement in cancer patients and its efficacy would likely be limited. To our knowledge, currently only one study is evaluating this type of strategy in AIC prevention [42].

Exercise as cardiac non-ischemic preconditioning has been proposed [43–45], but due to practical complexities for cancer patients, it is currently being tested in only one clinical trial with a suitable population [46]. Drug-based non-ischemic preconditioning has not been previously reported in AIC prevention clinical trials. A potential benefit of these interventions has been suggested by Serini et al., hypothesizing that omega-3 long-chain polyunsaturated fatty acids (EPA and DHA) could serve as cardio-protectors [47]. Cumulative evidence is not conclusive regarding the efficacy of EPA and DHA in primary, secondary and tertiary cardiovascular prevention [48, 49]. However, certain short-term interventions using high DHA doses reported attenuation of post-operative atrial fibrillation [50–52]. These effects would not be associated to omega-3 classical anti-inflammatory and antiplatelet mechanisms [53, 54], instead being based on indirect antioxidant properties [55]. Integration of DHA into cardiomyocytes induces a moderate peroxidation, weak to cause harm, though enough to activate the ROS-sensitive transcription factor Nrf2 which up-regulates antioxidant enzymes (non-hypoxic myocardial preconditioning) [56, 57]. Preclinical studies also reported the ability of n-3 long-chain fatty acids to prevent doxorubicin-induced ROS production and subsequent mitochondrial damage [57, 58].

Clinical evidence has reported DHA to be safe in metastatic breast cancer patients treated with doxorubicin [59]. Additionally, we performed a three-arm pilot protocol in patients with localized breast cancer, treated with adjuvant doxorubicin: one group with a DHA-enriched formula; another with carvedilol; and a double placebo group. Eleven patients were exposed to 2 g per day of EPA + DHA from 7 days before to 7 days after the initial chemotherapy cycle, without showing any side effects associated with the formula [60]. The DHA-enriched formula inhibited NT-proB-type natriuretic peptide (NT-ProBNP) plasmatic elevation after doxorubicin chemotherapy (48 h), suggesting a subclinical cardiotoxicity attenuation and showed a trend towards a lower LVEF decline at 10–12 months when compared to the placebo group. The lack of statistical significance was probably due to the small sample size and the limitations associated with echocardiographic sensitivity. The eleven patients exposed to 12.5 mg carvedilol every 12 h showed a significant reduction in LVEF drop at 10–12 months (51% less drop), compared to the placebo group. Unexpectedly, in this study arm, carvedilol did not impact the levels of NT-ProBNP. The study population was older and had at least one major cardiotoxicity risk factor.

In the present study, we hypothesized that breast cancer patients treated with anthracycline, preconditioned with DHA and carvedilol a week before the first chemotherapy cycle and for 90 days afterwards, will have less subclinical AIC, compared to comparable patients exposed to double placebo. We consider as subclinical AIC any manifestation of cardiac injury, such as: decrease of left ventricular function by a drop of LVEF by CMR, a decline in global longitudinal strain by two-dimensional ECHO, elevation of biomarkers or electrocardiographic alterations.

## Methods/design

### Trial design

CarDHA (Carvedilol-DHA trial) is a small, academic, randomized, double-blind, placebo-controlled, two-arm clinical trial created to test the utility of a non-hypoxic cardiac preconditioning intervention and carvedilol to prevent or attenuate subclinical manifestations of AIC.

It is supported by the Chilean National Commission for Scientific and Technological Research (CONICYT) and Clínica Alemana de Santiago. The study was initiated at San Juan de Dios Hospital in Santiago. Trial organization, management, data collection and analysis will be coordinated with clinical study staff at both centers. The co-authors have analyzed the study and agreed on this manuscript.

### Study population – patient selection and eligibility criteria

This study includes patients aged 18 to 75 years with localized breast cancer receiving chemotherapy at the oncology unit of San Juan de Dios Hospital. Specifically, patients with adjuvant and/or neoadjuvant systemic treatment with anthracycline-containing chemotherapy are included. At stages 1 and 2, verification by physical examination to exclude suspicion of metastasis is required. At stage 3, mammography/ultrasound or clinical examination via imaging staging with whole-body positron emission tomography- computed tomography (PET-CT) or abdominal thorax and pelvis CT with a bone scintigraphy is also required. Selection is open to all patients at the hospital who wish to participate and meet the eligibility criteria.

Inclusion criteria:
Women aged 18 to 75 yearsBreast cancer diagnosisEntering first cycle of chemotherapyPerformance status of 0–2 in the Eastern Cooperative Oncology Group (ECOG) scoreSubject must be willing and able to sign an informed consent

Exclusion criteria:
History of renal (serum creatinine greater than 2.0 mg/ml) or hepatic insufficiency (bilirubin> 3.0 mg/dl or serum albumin < 3.5 g/dl or prothrombin time < 60% in the absence of orally administered anticoagulant therapy or ultrasound signs of chronic liver damage)History of heart failureHistory of cardiac valvulopathyBaseline LVEF < 50% determined by transthoracic echocardiogramCardiogenic shockAny serious medical comorbidity that determines life expectancy as < 6 monthsCurrent participation in any other clinical investigationAny condition that contraindicates chemotherapy (i.e., pregnancy, lactation)History of severe adverse reaction to carvedilolHistory of severe adverse reaction to DHAPrevious treatment with β-blockers within the last 3 monthsUse of vitamin E, vitamin C or probucol, during the last 3 monthsUse of orally administered anticoagulantsHistory of coagulation disorders

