### Enrollment and baseline phase assessments

Patients diagnosed with localized breast cancer at the clinical campus are contacted by the study staff. After an initial clinical evaluation and explanation of the study protocol, patients agreeing to participate sign the informed consent followed by undergoing a baseline analysis including clinical evaluation and baseline laboratory and cardiovascular imaging to determine study eligibility. Baseline analyses are performed at least 10 days before the initial chemotherapy cycle, consisting of: (1) general laboratory testing, including blood cell count, INR/TTPA, full-biochemistry profile including serum creatinine and electrolytes; (2) plasma levels of NT-ProBNP and high-sensitivity cardiac troponin T (hs-cTnT); (3) resting electrocardiogram; (4) transthoracic echocardiogram; and (5) cardiac magnetic resonance. Breast cancer patients meeting the inclusion criteria are randomly allocated at a 1:1 ratio to either the intervention (DHA and carvedilol) or the control (double-placebo) arms. Randomization will be computer generated with homogeneous blocks of four by a specialist who is not related to the research group. The same person also assigns treatment and prepares the respective pillboxes with ad-hoc labeling and perform monitoring adherence. Patients, study staff, other care providers and data analysts are blinded to group allocation. The acquisition of the echocardiographic images will be performed by the same operator and will be reviewed by two other independent operators.

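### The only numeric renal exclusion limit is written as serum creatinine above 2.0 mg/ml (200 mg/dl), 100 times the same number per decilitre, so it would not operate on any plausible measured value

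*Protocol article*

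**What the plan says.** In the protocol article, under Study population – patient selection and eligibility criteria, one exclusion criterion covers both kidney and liver. It opens: "History of renal (serum creatinine greater than 2.0 mg/ml) or hepatic insufficiency". The hepatic part then sets its serum limits per decilitre: "bilirubin> 3.0 mg/dl or serum albumin < 3.5 g/dl".

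Under Enrollment and baseline phase assessments, the baseline work-up that decides eligibility includes a "full-biochemistry profile including serum creatinine and electrolytes". Creatinine is named again in the Follow-up protocol, as a test on days 2 and 4 after the first cycle, without a limit. The eligibility section is the only place where a creatinine limit appears.

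**The concern.** One criterion uses two volume units for serum concentrations: millilitres for creatinine, decilitres for bilirubin and albumin. The creatinine figure is the only numeric definition of renal insufficiency in the document, and it is meant to be compared with a value measured before randomisation. If the unit is wrong by a factor of 100, the comparison never leads to exclusion.

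What is at stake is safety screening and the description of the population. A numeric limit meant to keep patients with renal insufficiency out of the trial does not do so as printed. A reader who wants to repeat or pool the trial also cannot tell from the text which patients were eligible.

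**Working it through.** **Inputs, all from the protocol article**

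- Creatinine limit: above 2.0 mg/ml (eligibility criteria).
- Bilirubin limit: above 3.0 mg/dl (same criterion).
- Albumin limit: below 3.5 g/dl (same criterion).
- Baseline creatinine is measured and feeds the eligibility decision (Enrollment and baseline phase assessments).
- Planned sample 32 (Sample size and data analysis); 30 enrolled by 26 October 2018 (Trial status).

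**Step 1. Convert the printed limit.** 1 dl = 100 ml, so 2.0 mg/ml × 100 ml/dl = 200 mg/dl.

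**Step 2. Size of the discrepancy.** The same number written per decilitre would be 2.0 mg/dl. The ratio is 200 / 2.0 = 100. This measures the conflict only; it does not establish the intended limit.

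**Step 3. Set the three serum limits side by side.**

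| Analyte | As printed | Per decilitre |
|---|---|---|
| Creatinine | 2.0 mg/ml | 200 mg/dl |
| Bilirubin | 3.0 mg/dl | 3.0 mg/dl |
| Albumin | 3.5 g/dl | 3.5 g/dl |

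The criterion has no single mass scale, because albumin is in grams. What bilirubin and albumin share is the decilitre, and creatinine alone departs from it. The factor of 100 applies to the volume unit.

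**Step 4. Could a measured value reach the printed limit?** The document gives no range for creatinine, so this step is an assumption from general physiology: about 1 mg/dl in health, and in the tens of mg/dl at most in severe renal failure.

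- 1 mg/dl is 1 / 200 = 0.5% of the printed limit.
- 10 mg/dl is 10 / 200 = 5% of it.
- 99 mg/dl, the top of the tens, is 99 / 200 = 49.5% of it.

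Throughout this range the printed limit is not reached. The conflict of units in Steps 1 to 3 does not depend on the assumption.

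**Step 5. Look for a correction elsewhere.** There is none. The other mentions of creatinine name the test and give no limit.

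**The case against.** The strongest reply is that this is a transparent slip. Because the printed limit is so far out of reach, a clinician comparing a laboratory report with the figure 2.0 would hardly apply 200 mg/dl. The article also condenses a fuller protocol, and neither that protocol nor the screening form is shown; either may carry a consistent unit. With 30 of 32 patients enrolled by October 2018, a correction changes almost no future screening decision. All of this is fair, and it limits the practical harm. It does not remove the point: the article states a specific threshold, states it in a unit that conflicts with its neighbours, and ties creatinine to the eligibility decision.

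Four stronger readings are tempting, and the document does not support them.

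- **That the criterion excludes nobody with renal insufficiency.** It begins from a history of renal or hepatic insufficiency, with the number in parentheses, so a documented history can still exclude. Other exclusions, such as conditions that rule out chemotherapy, might catch some severe cases. Only the numeric limit fails.
- **That patients with renal impairment were randomised.** Nothing in the article shows a misclassified patient.
- **That one such patient could dominate the biomarker comparison in the third co-primary endpoint.** This needs an outside assumption about how NT-ProBNP and hs-cTnT depend on renal function. It also passes over two features of the plan: the endpoint is an elevation (for NT-ProBNP explicitly from baseline), which at least partly offsets a stably raised starting value, and non-normal variables go to medians and the Mann-Whitney test, where one extreme value has limited influence.
- **That the intended limit must be 2.0 mg/dl.** The text shows that the units conflict, not which limit was meant.

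**Conclusion.** The point holds for the numeric limit. As printed it is 200 mg/dl, 100 times the same number per decilitre, and would not act on any plausible measured creatinine. The conversion and the conflict of units are certain from the text; that no patient reaches the limit rests on general physiology. The route through a documented history of renal insufficiency remains open.

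This is an error in an operative eligibility threshold, so it needs correcting and its use at screening needs verifying. It has no shown effect on sample size, power or the planned analyses, and no shown effect on any patient.

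**What to change.** The sponsor should:

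1. Reconcile the creatinine unit and limit with the full protocol and with what was applied at screening, and confirm which limit was intended. That choice is the sponsor's.
2. Correct the article accordingly, and also the full protocol and screening form if they carry the same conflict.
3. Check the baseline creatinine of every enrolled patient against the confirmed limit and list any eligibility deviation.

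The cost is small: a change of a few characters in the text, and a check of 30 to 32 laboratory values that the baseline assessment already requires. No new data are needed and the analysis does not change.

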### Enrollment and baseline phase assessments

Patients diagnosed with localized breast cancer at the clinical campus are contacted by the study staff. After an initial clinical evaluation and explanation of the study protocol, patients agreeing to participate sign the informed consent followed by undergoing a baseline analysis including clinical evaluation and baseline laboratory and cardiovascular imaging to determine study eligibility. Baseline analyses are performed at least 10 days before the initial chemotherapy cycle, consisting of: (1) general laboratory testing, including blood cell count, INR/TTPA, full-biochemistry profile including serum creatinine and electrolytes; (2) plasma levels of NT-ProBNP and high-sensitivity cardiac troponin T (hs-cTnT); (3) resting electrocardiogram; (4) transthoracic echocardiogram; and (5) cardiac magnetic resonance. Breast cancer patients meeting the inclusion criteria are randomly allocated at a 1:1 ratio to either the intervention (DHA and carvedilol) or the control (double-placebo) arms. Randomization will be computer generated with homogeneous blocks of four by a specialist who is not related to the research group. The same person also assigns treatment and prepares the respective pillboxes with ad-hoc labeling and perform monitoring adherence. Patients, study staff, other care providers and data analysts are blinded to group allocation. The acquisition of the echocardiographic images will be performed by the same operator and will be reviewed by two other independent operators.

